### Sample size

The underpinning feasibility study showed that recruitment to an original planned cluster randomised trial would require recruitment of over 40 hospitals and was unlikely to be achieved. Consequently, the design was changed to a stepped wedge due to the increased power provided by this design.

With a baseline step with all hospitals receiving the control followed by four separate steps, each randomising five hospitals to switch from control to intervention (20 hospitals in total) will have 89.5% power to detect a difference of 16.7% to 13.7% of 90-day re-admission rates assuming a 5% level of significance and an intra-class correlation coefficient (ICC) of 0.05 and 200 participants per hospital per step. The total sample size will be 20 000 participants. The anticipated 3% difference is similar, but slightly smaller, to the difference reported in the MedSafer study.^19^

From our feasibility study findings, we estimate that 10% of patients on study wards or consultees will provide written (or, if required, virtual) informed consent for additional patient-reported outcome data. For the enhanced data collection period, where medication changes are recorded in hospital, then if the sites collect data on 60 participants in each of the enhanced data collection periods, the study will have 99.99% power to detect an average change of 0.5 medications between the control and intervention phase, assuming a SD of 1.5 medications, a 5% level of significance and an ICC of 0.05.

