### Recruitment

All patients receiving treatment under the care of participating geriatricians on the study wards within the study window (1 February 2024 to 31 July 2025) will be eligible for inclusion.

With national CAG^20^ permission, all patients admitted to wards under the care of participating consultant geriatricians will be enrolled for routine data collection purposes, enabling collation of the primary outcome measure for all patients. Consequently, we will not be required to enact any strategies for achieving adequate participant enrolment.

During enhanced data collection periods, 1 month during the control period and 1 month during the intervention period, patients admitted to wards under the care of participating consultant geriatricians will be approached to be consented for enhanced data collection, that is, non-routinely collected data needed for secondary outcome measures and process evaluation purposes.

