### Data collection and management

#### Plan for assessment and collection of outcomes

We will collect relevant outcome data at two levels for patients admitted to study wards and under the care of participating consultant geriatricians:

Routinely collected data for all patients admitted for the duration of control and intervention steps, that is, 18 months.Non-routinely collected data during ‘enhanced data collection periods’ which take place for 4 weeks during both the control and intervention period.

Routine data will be collected by nurses employed within the national RDN^16^ for all patients under the care of a participating geriatrician admitted to the study wards during the trial period and provided anonymously to the research team following national CAG^20^ permission to collect these data without the requirement for patient consent.

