#### Additional analyses

A sensitivity analysis will adjust for relevant baseline characteristics, that is, age and the number of pre-admission medicines.

The number of medications stopped during the enhanced data collection period will be compared between the control and intervention using a linear mixed model including hospital as a random effect, and fixed factors will include randomisation arm and time period.

The proportion of patients per arm where a pre-admission medicine is proactively deprescribed will be compared using logistic regression, the same model as above.

The QoL measures will be compared between the control and intervention using a linear mixed model including hospital as a random effect, and fixed factors will include randomisation arm and time period.

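### The 99.99% power quoted for a 0.5-medication change is not delivered by two enhanced months per hospital under the stated arm-plus-period model

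*Protocol article*

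**What the plan says.** The Sample size section of the protocol article makes a second power statement besides the one for readmission: "the study will have 99.99% power to detect an average change of 0.5 medications between the control and intervention phase". Its stated inputs are a standard deviation of 1.5, an ICC of 0.05, a 5% test and 60 patients per hospital in each of the enhanced periods.

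Three other sections fix what that figure must rest on:

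- **Sampling.** Recruitment places enhanced collection at "1 month during the control period and 1 month during the intervention period". The section on the plan for assessment and collection of outcomes agrees, with periods "which take place for 4 weeks during both the control and intervention period". Each hospital therefore contributes two cells of data.
- **Calendar.** Trial design has four groups of five hospitals stepping at 3-month intervals. Each has a 3-month implementation phase before the active phase, and each site takes part for 18 months, which is six quarters.
- **Model.** Under Additional analyses, "The number of medications stopped during the enhanced data collection period will be compared between the control and intervention using a linear mixed model" that has hospital as a random effect and arm and time period as fixed factors. The proactive-deprescribing and quality-of-life comparisons use the same terms.

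The text does not say in which quarters the two enhanced months fall. That is presumably in Figure 1, which was not available for this review.

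**The concern.** A stepped wedge with fixed period effects separates the intervention from calendar time mainly through periods in which some hospitals are active while others are still control. The implementation phase narrows that overlap. Group g is control in quarters 1 to g, implementing in quarter g+1 and active from quarter g+2. Control and active hospitals therefore coexist only in quarter 3 (group 1 active; groups 3 and 4 control) and quarter 4 (groups 1 and 2 active; group 4 control). With only two sampled cells per hospital, little of even this overlap may be observed, and what is observed is mostly a comparison between different hospitals.

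A power of 99.99% tells the reader that this comparison is beyond doubt. Medication change is the direct evidence that the intervention altered prescribing, and it will be needed to interpret whatever is found on readmission. If the margin is really a conventional one, or if the calendar does not identify the arm effect, that should be known before the data are analysed.

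**Working it through.** **Inputs.** From Sample size: difference 0.5, SD 1.5, ICC 0.05, 5% significance, 60 per hospital per enhanced period, 20 hospitals in four groups of five. From Recruitment: one control cell and one intervention cell per hospital. From Trial design: six quarters with a one-quarter implementation gap. From Additional analyses: hospital random, arm and period fixed. Assumptions of this check: two-sided test, normal approximation, period taken as categorical quarters unless stated otherwise.

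**Variance components.** Total variance 1.5² = 2.25. Between hospitals: 0.05 × 2.25 = 0.1125. Within hospitals: 0.95 × 2.25 = 2.1375, so 2.1375/60 = 0.035625 per cell mean. Power = Φ(0.5/SE − 1.96). Reaching 99.99% needs 0.5/SE = 1.960 + 3.719 = 5.679, so SE ≈ 0.088.

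**Can the stated figure be reproduced?**

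| Assumption | SE | Power |
|---|---|---|
| Before-after within 20 hospitals, no period term: √(2 × 0.035625/20) | 0.0597 | above 99.99% (0.5/SE = 8.4) |
| Wedge without gap, 5 periods, 60 in every period | 0.0676 | above 99.99% |
| Wedge with gap, 6 periods, 60 in every non-implementation quarter | 0.0896 | 99.985% |

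The last row rounds to 99.99%, but it needs five sampled quarters per hospital instead of two. The method itself is not in question. Applied to the primary outcome (200 per hospital per step, variance 0.167 × 0.833, five periods), it gives 89.54% against the stated 89.5%.

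**Stated sampling with the stated model.** Take the last control quarter and the first active quarter: group 1 in quarters 1 and 3, group 2 in 2 and 4, group 3 in 3 and 5, group 4 in 4 and 6. Quarters 1, 2, 5 and 6 each hold one cell type from one group, so their period effects absorb those cells. What remains is quarter 3 (group 1 active against group 3 control) and quarter 4 (group 2 active against group 4 control), that is, ten active against ten control cells from different hospitals:

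- variance of a cell mean = 0.1125 + 0.035625 = 0.148125
- SE = √(2 × 0.148125/10) = √0.029625 = 0.172
- power = Φ(0.5/0.172 − 1.96) = Φ(0.945) = 82.8%

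**Other calendars.** Because the real one was not seen, generalised least squares was run over every admissible choice of quarters. The covariance of a hospital's two cell means was 0.1125 in every entry plus 0.035625 on the diagonal.

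- *Timing common within a group.* Group g has g control quarters and 5 − g active quarters to choose from, so there are (1×4)(2×3)(3×2)(4×1) = 576 schedules. The best has SE 0.158 and power 88.6%. The median of the 140 estimable schedules is about 68%.
- *Not estimable.* In the other 436 the arm effect cannot be separated from period. The plainest case is all control months in quarter 1: arm then equals not being in quarter 1. All active months in quarter 6 fails in the same way.
- *Timing free for each hospital.* The best found by local search has SE 0.150 and power 91.4%.
- *Linear time trend instead of categorical period.* 89.3% for last-control/first-active and 98.2% at best with group-common timing.
- *Implementation gap ignored (five periods).* At best 99.94%, and not the stated design.

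**The case against.** **The calendar is in a figure that was not seen, and period may be defined differently in the SAP.** Both are true, and they limit what can be claimed. Power for the real calendar cannot be given here, and a linear trend would cost less than categorical quarters. The conclusion about 99.99% survives, because no calendar examined reaches it under either form of period.

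**The count of non-estimable schedules is not a probability.** This stands. A reader might infer from 436 of 576 that the planned model will probably fail. The documents do not support that: the count weights impractical schedules equally with sensible ones, and a natural choice (last control, first active) is estimable.

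**The error may not be an omitted period term.** This also stands. It is tempting to infer that the sponsor powered a simple before-after comparison, but that gives a power indistinguishable from 100%. Counting 60 patients in every non-implementation quarter comes closer to the printed figure. Neither origin is documented.

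**Sixty per month may be out of reach with 10% consent.** A reader might carry the 10% consent estimate over to medication counts and conclude that power collapses. The Sample size section ties that estimate to patient-reported data. Table 1 takes medicine counts from routine hospital records, and its footnote describes Section 251 approval where consent or assent was not possible. Sixty per cell is therefore kept throughout this check.

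**The outcome is secondary, and power can still exceed 80%.** Correct, and it sets the weight of the point.

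**Conclusion.** The point holds as an overstated power figure for a secondary outcome. Under the sampling, the implementation gap and the model that the protocol article itself states, power for a 0.5-medication change is 82.8% with last-control/first-active timing, at most 88.6% with group-common timing and about 91% with the best hospital-specific timing found. Under a linear trend it is at most about 98%. Some calendars give no estimate of the arm effect at all; whether the actual calendar is one of them cannot be judged without Figure 1.

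This rests on a two-sided 5% test, 60 patients per cell, the stated SD and ICC, and a single hospital random effect. The 91% comes from a search and is not a proven maximum. A correlation that decays between periods within a hospital, or monthly periods, would lower the figures further.

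The estimability question also reaches the proactive-deprescribing and quality-of-life comparisons, which share the model terms. The primary analysis of readmission uses data from all control and intervention periods and is not affected.

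**What to change.** 1. Recalculate the power for medications stopped under the arm-plus-period model, using the actual enhanced-data calendar in Figure 1, and replace the 99.99%. State how period is coded and whether the test is two-sided.
2. Before analysis, confirm from that calendar that the arm effect is estimable with the period term, for this outcome and for the others that share the model.
3. If it is not, pre-specify in the SAP a hospital-adjusted comparison of the intervention and control months with a linear-trend sensitivity analysis, and report the result as before-after evidence.

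The cost is one recalculation and a few lines in the SAP. The quoted power becomes less favourable. No data collection changes and the sample size is untouched.

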### Recruitment

All patients receiving treatment under the care of participating geriatricians on the study wards within the study window (1 February 2024 to 31 July 2025) will be eligible for inclusion.

With national CAG^20^ permission, all patients admitted to wards under the care of participating consultant geriatricians will be enrolled for routine data collection purposes, enabling collation of the primary outcome measure for all patients. Consequently, we will not be required to enact any strategies for achieving adequate participant enrolment.

During enhanced data collection periods, 1 month during the control period and 1 month during the intervention period, patients admitted to wards under the care of participating consultant geriatricians will be approached to be consented for enhanced data collection, that is, non-routinely collected data needed for secondary outcome measures and process evaluation purposes.

### Assignment of interventions: allocation

#### Sequence generation

Sites will be randomised to the four ‘groups’, the ‘groups’ being the step at which they started the intervention. Group 1 will start the intervention on the first step, etc. A fifth group, Group 5, is the reserve list. To ensure no two sites from the same region are randomised to the same group and thereby overwhelm the local RDN team, randomisation will be stratified by region. A block size of 4 will be used so that randomisation could occur once four sites are recruited and concealment maintained.

#### Concealment mechanism

Randomisation will occur after every fourth site is recruited. If sites from the same region are participating, randomisation will be delayed until they can all be randomised at the same time. This process ensures concealment as the recruitment team will be unable to predict treatment allocation.

#### Implementation

The list will be generated using the Sealed Envelope online randomisation list generator. Sites will be recruited and once four sites confirm capability and capacity to deliver the research, they will be allocated to an intervention step by the trial manager using the REDCap^21^ randomisation system.

#### Blinding

Due to the nature of the intervention and trial design, blinding to allocation is not possible.

### Data collection and management

#### Plan for assessment and collection of outcomes

We will collect relevant outcome data at two levels for patients admitted to study wards and under the care of participating consultant geriatricians:

Routinely collected data for all patients admitted for the duration of control and intervention steps, that is, 18 months.Non-routinely collected data during ‘enhanced data collection periods’ which take place for 4 weeks during both the control and intervention period.

Routine data will be collected by nurses employed within the national RDN^16^ for all patients under the care of a participating geriatrician admitted to the study wards during the trial period and provided anonymously to the research team following national CAG^20^ permission to collect these data without the requirement for patient consent.

#### Plans to promote participation retention and complete follow-up

With enrolment of all patients and collation of routinely collected data, there are no plans to promote participation retention for the purposes of the primary outcome measure.

Due to the short duration of the follow-up period, 3 months (90 days) following discharge, the likelihood of drop-out by patients is minimal. However, as participants will be followed up in the community post-discharge, there is a potential for loss to follow-up. Participants who agree to complete the study questionnaires will be asked to provide contact information to be contacted at the 3 months follow-up time point—telephone, postal address and/or email. Patients who do not respond to contact requests to complete follow-up questionnaires by telephone will be considered as lost to follow-up for the purposes of questionnaire completion. However, routine clinical data will still be collected from patient records. Data will be retained for analysis.

#### Data management

Data will be entered under the participant’s ID onto the central database stored on NCTU servers. Access to the database will be via unique, individually assigned usernames and passwords, and only accessible to members of the CHARMER research team NCTU and external regulators if requested. The servers are protected by firewalls and are patched and maintained according to best practice. The physical location of the servers is protected physically and environmentally in accordance with University of East Anglia’s General Information Security Policy 3 (GISP3: Physical and environmental security).

The database has been developed by NCTU Data Management using REDCap,^21^ in conjunction with the CHARMER trial team. The database software provides several features to help maintain data quality, including maintaining an audit trail, allowing custom validations on all data, allowing users to raise data query requests and data quality rules to identify validation failure/missing data.

After completion of the study, the database will be retained on the servers of NCTU for ongoing analysis of secondary outcomes.

#### Confidentiality

All data will be sent to the Clinical Trials Unit which will be responsible for data analysis. Data will be stored in password protected computers and only shared in an anonymous format with the wider research team.

### Statistical methods for primary and secondary outcomes

#### Characterising and comparing sites

Participating hospitals and geriatricians and pharmacists will be characterised using descriptive statistics from the hospital site profile questionnaire and practitioner participant demographic questionnaire. Data will be visually compared with data captured from NHS Improvement’s hospital provider level benchmarking tool ‘model hospital’^22^ regarding the number and cost of staff on medicine for older people’s medicine wards. Demographic characteristics of patients between all study wards of the participating hospitals will be visually compared to explore whether they are comparable. For the sample of patients in the study cohort from whom consent is obtained either from the patient or consultee for additional non-routine data to be collected, the demographic characteristics of this group will be visually compared with the wider study cohort. This will establish whether the sub-set of patients for whom additional data are collected is a good representation of the patient cohort in the study.

#### Main effectiveness analysis

The primary analysis will be using intention-to-treat with a pre-specified statistical analysis plan (SAP) agreed prior to analysis. Analysis will be at the patient level and include data from all patients.

Unplanned readmission at 90 days, primary outcome measure, will be compared between the treatment and control groups using a logistic mixed regression model with hospital included as a random effect, and fixed factors will include randomisation arm and time period. If a significant number have more than one readmission, then a Poisson or Negative binomial model will be used as a secondary analysis. The assumptions of the models will be checked and, if appropriate, a Generalised Estimating Equation approach will be used if the random effect is not normally distributed, or a non-parametric bootstrap approach will be used to account for missing data.

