A hospital action plan to set deprescribing as an organisational goal to be achieved by implementing the remainder of the CHARMER intervention components.A geriatrician workshop with pre-prepared videos of peers navigating challenging deprescribing discussions with patients and relatives.A pharmacist workshop with case studies to address negative beliefs about the consequences of deprescribing.Weekly pharmacist and geriatrician briefings to identify opportunities for proactive deprescribing.Weekly benchmarking reports on deprescribing activities to allow sites to compare their performance against other sites.

In line with the UK Medical Research Council guidance for developing and evaluating complex interventions,^14^ the CHARMER intervention and trial design were feasibility tested.^15^ This led to numerous changes to both intervention implementation support and trial design, with the most significant being the decision to move from a cluster RCT to a cluster randomised stepped-wedge design. Due to the increase in power associated with a stepped-wedge design, this change requires half the number of hospitals for the trial representing more efficient trial design and thus better value for money. Furthermore, this design provides longer term follow-up data in a proportion of intervention hospitals and will thereby allow us to assess whether the intervention is normalised.

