### Trial design

Cluster randomised stepped-wedge design trial with internal pilot. A maximum of 24 hospitals (20 active, four reserve) across England will be recruited to take part. All participating hospitals will begin the trial at the same time in a control phase.

We will step hospital sites into the intervention ‘implementation phase’ at 3 month intervals (five hospitals every 3 months in four steps). The intervention ‘implementation phase’ will last for 3 months for all hospitals, prior to transferring into the active intervention phase. Each site will therefore take part in the trial for a total of 18 months (with an additional 3-month follow-up period for data collection). This is summarised in figure 1.

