### Hospitals

Inclusion

Acute hospital.Provide an older people’s medicine service with at least one inpatient ward on which to conduct the CHARMER trial (the study ward).The majority of patients on the study ward(s) have a minimum length of stay of 3 days.The average total monthly throughput across study ward(s) of approximately 100 patients has at least one geriatrician (consultant or specialist registrar) and at least one ward-based pharmacist working on them.There is an electronic prescribing system on the study ward(s).The hospital is willing and has the capability and capacity to implement the five components of the CHARMER intervention.Able to provide a 0.2 whole time equivalent Project Manager to oversee implementation of the CHARMER intervention over a 14-week period (3 month implementation phase and 2 weeks within the active intervention phase).Named clinician willing and appropriate to take PI responsibility.Suitably trained staff, for example, sufficient research nurses, to recruit patient and personal consultee participants and enter required data.

Exclusion

Wards that primarily host patients who are medically fit for discharge and awaiting discharge care packages.Hospitals without a ward-based pharmacy service.Mental health hospitals.Hospitals that implemented the intervention in the feasibility study.

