#### Intervention description

The intervention is summarised in the background and described in detail in a separate publication.^10^ The action plan and geriatrician and pharmacist workshops will be delivered during the 3-month implementation phase. The weekly briefings and benchmarking reports will occur throughout the active intervention phase.

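### The single arm term assumes a constant effect after go-live; in this layout the first active quarter dominates the estimate, so an exposure-time model should be pre-specified beside it

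*Protocol article*

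**What the plan says.** The protocol article, under Main effectiveness analysis, compares unplanned readmission at 90 days "using a logistic mixed regression model with hospital included as a random effect, and fixed factors will include randomisation arm and time period". The only sensitivity analysis named for this outcome, under Additional analyses, adjusts for age and number of pre-admission medicines. No stated term depends on time since go-live.

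The Trial design section steps in "five hospitals every 3 months in four steps". It adds: "The intervention ‘implementation phase’ will last for 3 months for all hospitals, prior to transferring into the active intervention phase". It also says: "Each site will therefore take part in the trial for a total of 18 months".

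Three other places bear on whether the effect is constant:
- Background and rationale says the longer follow-up in some hospitals "will thereby allow us to assess whether the intervention is normalised".
- Intervention description places the action plan and workshops in the implementation phase, and continues: "The weekly briefings and benchmarking reports will occur throughout the active intervention phase".
- The hospital eligibility criteria require a part-time Project Manager "over a 14-week period (3 month implementation phase and 2 weeks within the active intervention phase".

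**The concern.** Part of the intervention is delivered once, before the active phase. Required Project Manager support ends two weeks into that phase, while briefings and benchmarking continue. The effect could build up as practice changes, or fade as support ends. The protocol does not claim either, but it does want to know whether the intervention becomes normal practice.

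With one arm term and categorical period effects, a stepped-wedge estimate averages the quarter-specific effects evenly only if those effects are equal. Otherwise the layout sets the weights, and these can be very uneven or negative. At stake are a benefit that takes time to appear being reported as little or nothing, a short-lived benefit being reported as larger than any quarter's true effect, and a persistence question that the stated primary model cannot address.

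**Working it through.** **Inputs.** From the protocol: 4 groups of 5 hospitals, 200 patients per hospital per step, ICC 0.05, 16.7% versus 13.7%, 5% level (taken as two-sided), 18 months = 6 quarters, one implementation quarter per hospital. My assumptions: equal quarter sizes, no effect before go-live, and a linear (risk-difference) approximation to the logistic model.

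**Layout** (C control, I implementation, A1 to A4 active quarters):

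| Group | Months 0-3 | 3-6 | 6-9 | 9-12 | 12-15 | 15-18 |
|---|---|---|---|---|---|---|
| 1 | C | I | A1 | A2 | A3 | A4 |
| 2 | C | C | I | A1 | A2 | A3 |
| 3 | C | C | C | I | A1 | A2 |
| 4 | C | C | C | C | I | A1 |

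**Model.** Generalised least squares on hospital-quarter means, with period effects, one arm term and a hospital random intercept. The covariance within a hospital is V = [σ²(1-ρ)/m] I + σ²ρ J, with σ² = 0.167 × 0.833 = 0.139, ρ = 0.05 and m = 200.

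**The plan's own figure first.** Sample size states "89.5% power to detect a difference of 16.7% to 13.7% of 90-day re-admission rates". A five-quarter layout without an implementation quarter gives SE 0.933 points and power Φ(3/0.933 - 1.96) = 89.5%, so the stated figure is reproduced. In that layout the weights for A1 to A4 are already +0.99, +0.30, -0.09, -0.19.

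**Weights in the six-quarter layout.** The expected estimate is Σ wₖδₖ, where δₖ is the true effect in active quarter k and wₖ sums the estimator's cell weights for that quarter. With implementation quarters excluded:
- A1: 0.500 + 0.331 + 0.162 + 0.242 = +1.235
- A2: 0.169 + 0.000 + 0.081 = +0.250
- A3: -0.162 - 0.081 = -0.242 (rounded cells)
- A4: -0.242

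The weights sum to 1. The negative ones arise because months 12-18 then contain no control cells. Hospitals that went live earlier act as comparators for those that went live later.

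| Implementation quarters | A1 | A2 | A3 | A4 | SE (points) |
|---|---|---|---|---|---|
| Excluded | +1.235 | +0.250 | -0.242 | -0.242 | 1.235 |
| Coded as control | +0.893 | +0.300 | -0.047 | -0.147 | 0.89 |

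With exclusion, an ICC of 0.01 gives +1.18, +0.25, -0.21, -0.21, and an ICC of 0.10 gives +1.24, +0.25, -0.25, -0.25. A check on the logit scale gives +1.25, +0.25, -0.25, -0.25.

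**Patient average.** A1 is seen in four groups, A2 in three, A3 in two and A4 in one, so the average is 0.4δ₁ + 0.3δ₂ + 0.2δ₃ + 0.1δ₄.

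**Expected estimates** (reductions in percentage points):

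| True effect A1/A2/A3/A4 | Patient average | Excluded | As control |
|---|---|---|---|
| 3/3/3/3 | 3.0 | 3.0 | 3.0 |
| 2.5/3/3/3 | 2.8 | 2.38 | 2.55 |
| 3/2.5/2/2 | 2.55 | 3.36 | 3.04 |
| 1.5/3/3/3 | 2.4 | 1.15 | 1.66 |
| 0.75/1.5/2.25/3 | 1.5 | 0.03 | 0.58 |
| 0/3/3/3 | 1.8 | -0.70 | +0.32 |
| 3/1.5/0/0 | 1.65 | 4.08 | 3.13 |

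Example, row five, excluded: 1.235 × 0.75 + 0.250 × 1.5 - 0.242 × 2.25 - 0.242 × 3 = 0.03.

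With exclusion, power for 1.5/3/3/3 is Φ(1.15/1.235 - 1.96) = 15%. For 0/3/3/3 the estimate lies 0.70/1.235 = 0.57 SE on the wrong side of zero, so the likely report is an inconclusive result, not a significant harm.

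**Exposure-time model.** With one effect per active quarter and implementation quarters excluded, the patient-averaged effect has SE 1.72 points. Power for a constant 3 points is Φ(3/1.72 - 1.96), about 42%. The single term has Φ(3/1.235 - 1.96), about 68%, in the same layout.

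**The case against.** The arithmetic is not in dispute; its reach is.

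**Coding.** The protocol does not say implementation quarters are excluded, and it says data from all patients are included. Exclusion is an inference from 20 000 = 20 × 5 × 200, which counts five of six quarters. Coded as control, 0/3/3/3 no longer reverses sign and the gradual build-up no longer vanishes. This stands: the exact weights depend on the coding. Dominance of the first active quarter, with low or negative weight later, holds under both. Coding these patients as intervention would put a weight of +0.89 on the implementation quarter itself, which is a different problem.

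**Severity of the scenarios.** Workshops precede the active phase, so 0/3/3/3 means about six months from stepping in with no effect, then the full effect at once. Milder trends do less damage. This stands too.

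**Evidence for a trend.** The 14 weeks of Project Manager time is what a hospital must be able to provide; it does not show that support stops then. The passages justify examining the effect over time, not predicting its shape.

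**Normalisation.** A reader might infer that the protocol contradicts itself here. It does not assign that question to the primary model, and the process evaluation is reported separately.

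**The SAP.** This is a standard stepped-wedge model. The SAP takes priority over the protocol and may already add an exposure-time analysis. That makes correction easy, but the article does fix the estimator, and the model checks it names concern the random effect and missing data, not a changing effect.

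**Conclusion.** The point holds as a worthwhile, inexpensive improvement. As fixed in the article, the arm coefficient is not an average of the active-quarter effects. Weights are about +1.24, +0.25, -0.24, -0.24 with implementation quarters excluded, or +0.89, +0.30, -0.05, -0.15 with them coded as control. Marked build-up is strongly attenuated and marked fading is inflated. Under these two codings mild trends give smaller bias (2.38 or 2.55 against 2.8; 3.36 or 3.04 against 2.55), and a constant effect gives none.

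A reader might infer that the primary result will vanish or change sign whenever the effect changes over time, or that the constant-effect test must be replaced. The documents support neither. Sign reversal needs a severe delay and, between these two codings, occurs in the scenarios above only with exclusion. If there is no effect in any quarter, the single-term test remains a fair test of that.

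The figures assume equal quarters of 200, no effect before go-live and the stated ICC with no decay over time.

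**What to change.** Under Main effectiveness analysis, or in the SAP before any outcome data are analysed:

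1. Keep the constant-effect model as the primary test.
2. State whether implementation-phase patients are excluded, coded as control or given their own level.
3. Pre-specify a supporting model for the primary outcome with a separate effect for each active quarter since go-live. Report the four effects and the patient-averaged effect with its CI.
4. State that the single odds ratio is not read as the average effect if the quarter-specific effects show a trend, and that any readmission-based statement on persistence rests on the supporting model.

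**Cost.** This takes a few sentences and one extra model on data already collected. The averaged estimate is less precise: SE about 1.7 versus 1.2 points with implementation quarters excluded, and about 42% power for a constant 3 points. The loss is smaller if those quarters are coded as control. The fix improves interpretation only; the low power of the retained primary test under a delayed effect is not cured.
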